### Adverse event

Participants will be instructed to immediately report any adverse events occurring during the study. Exercise termination will follow the American College of Sports Medicine (ACSM) standard guideline (e.g., moderate to severe chest pain, severe or unusual shortness of breath, etc.) [44].

### Assessment and outcome measures

Demographic data of the participants which consisted of age, gender, body mass index (BMI), education level, medical conditions, diet, supplements, lipid profile (high-density lipoprotein cholesterol (HDL), total cholesterol, low-density lipoprotein cholesterol (LDL)), glucose level (Fasting Blood Sugar-FBS) and history of falls in the past year will be obtained. Primary outcome measures will be cognitive performance. Secondary outcomes will be plasma biomarkers via ELISA assays (including BDNF, IL-6, irisin, and FGF21) and physical performance. All assessments will be administered at baseline and post 12-week intervention (Table 2).

**Table 2 Tab2:** Schedule of enrolment, interventions, and measurements for outcome measures

	Study period			
	**Enrollment**	**Allocation**	Post allocation	**Post-intervention**
**Timepoint**	-T1	T0	0–12 weeks	T1 (12 weeks)
**Enrollment**:				
Eligibility screen	x			
Informed consent	x			
Allocation		x		
**Interventions**:				
Exercise group			↔	
Control group			↔	
**Measurement**:				
ADAS-Cog		x		x
LMT		x		x
TMT		x		x
BDNF		x		x
IL-6		x		x
Irisin		x		x
FGF21		x		x
TUG		x		x
30-s CST		x		x

### Primary outcomes

Primary outcome measures will be cognitive function (global cognition, executive function, memory, and attention). Alzheimer’s Disease Assessment-cognitive subscale (ADAS-Cog) has been verified to be useful in screening cognitive function among individuals with MCI [45]. ADAS-Cog will be used to evaluate the participant’s global cognitive function. The ADAS-Cog assesses performance on 11 cognitive tasks: orientation, a 10-word list learning task, a 12-word recognition task, recall of instructions, comprehension of commands, object and finger naming, word-finding difficulty, expressive language, language comprehension, ideational praxis, and constructional praxis. Individual items and the total score will be recorded. Logical memory test (LMT), a subtest of the Wechsler Memory Scale will be used to evaluate episodic memory. Participants will be asked to listen carefully to 2 short stories and remember their content. After a 30-minute delay, they will be asked to repeat each story as accurately as possible. A score is assigned based on the number of correct details recalled. The Trail Making Test (TMT) will be used to assess attention (part A) and executive function (part B-A). In TMT part A, participants will be instructed to draw a line to connect consecutive numbers in numerical order (e.g., 1-2-3) as quickly and correctly as possible. For TMT part B, participants will be asked to draw a line to connect consecutive numbers in numerical order and letters in alphabetical order in an alternating sequence as quickly and correctly as possible. The time taken to complete TMT part A will be used to evaluate attention and the time difference between parts B and A will be used to assess executive function.

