### Sample size calculation

The sample size for the study was determined for the primary outcome measures based on previous studies that examined the effects of Tai Chi which could be considered as combined physical-cognitive exercise at low-to-moderate intensity [48, 49]. The previous findings on memory and executive function yielded effect sizes of 0.40 and 0.38, respectively [49]. Thus, the sample size was estimated using the lowest effect size (i.e., executive function). With 80% power and 5% type I error, a total sample size of 57 (29 per group) will be required to detect change. To accommodate 10% dropout, a total of 64 participants (32 per group) will be enrolled in the study.

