### Statistical analysis

Data normality will be performed using the Shapiro-Wilk test. Descriptive statistics will be used to describe the demographic characteristics of the participants. If data are normally distributed, the independent samples t-test (for continuous data) and chi-square test (for categorical data) will be conducted to determine differences in demographic data between the intervention and control groups at baseline. A two-way mixed-model ANOVA will be used to compare the outcome measures across the two different assessment intervals (at baseline and the end of 12 weeks) and between the two groups (exercise and control groups). Bonferroni will be used for the post-hoc analysis in this study. However, if data are not normally distributed, non-parametric statistics will be performed. Specifically, the Mann-Whitney U test will be used for pairwise comparisons between groups, and the Wilcoxon signed-rank test will be used to compare the outcome measures between baseline and the end of 12 weeks. Data in this study will be analyzed using the intention-to-treat (ITT) approach. Missing data will be handled using multiple imputations. The alpha level will be set at 5%.

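### Four unranked primary cognitive outcomes share an undivided 5% alpha with no success rule across them; if any one positive result counts, the false-positive risk exceeds 5% and can reach 18.5%

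*Protocol article*

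**What the plan says.** All references are to the protocol article.

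- **Primary outcomes:** "Primary outcome measures will be cognitive function (global cognition, executive function, memory, and attention"). Global cognition is measured by ADAS-Cog, for which "Individual items and the total score will be recorded". For memory, "Logical memory test (LMT), a subtest of the Wechsler Memory Scale will be used to evaluate episodic memory". For the other two domains, "The Trail Making Test (TMT) will be used to assess attention (part A) and executive function (part B-A"). This makes four endpoints. None is called the main one, and no composite is defined.
- **Statistical analysis:** a two-way mixed ANOVA (group by time) is applied to the outcome measures, with rank-based tests if normality fails. Then "Bonferroni will be used for the post-hoc analysis in this study". The section closes with "The alpha level will be set at 5" per cent.
- **Sample size calculation:** "The previous findings on memory and executive function yielded effect sizes of 0.40 and 0.38, respectively". The smaller value, for executive function, was used: "With 80% power and 5% type I error, a total sample size of 57 (29 per group) will be required to detect change". Enrolment is 64, to allow for 10% dropout.
- **Discussion:** the primary aim is a single general question about the effect on cognitive function.

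**The concern.** The article fixes three things that have to fit together: which outcomes are primary, the error rate, and the sample size. With four primaries, 5% can describe the error rate of each test or of the trial's overall conclusion. It cannot describe both unless a rule links the four results to that conclusion, and the article gives none.

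The Bonferroni sentence does not clearly fill the gap. It follows directly on the ANOVA and is limited to post-hoc analysis, so it most naturally means follow-up comparisons within one outcome's ANOVA.

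At stake is the headline inference. Without a rule, it can be settled after the results are seen whether one, some or all of the four domains were needed to say that the exergame improves cognition. If one is enough, the 5% used to size the trial is not the error rate of that conclusion.

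**Working it through.** **1. Inputs from the protocol article.** Four primary endpoints (Primary outcomes). Alpha 0.05, not divided (Statistical analysis). Effect size 0.38, power 80%, total 57, dropout 10%, enrolled 64 (Sample size calculation). The metric of 0.38 and the correlations among the four outcomes are not given.

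**2. Reproducing the planned 57.** Read 0.38 as Cohen's f in a two-group F test, with 1 and N − 2 degrees of freedom and noncentrality f² × N.
- N = 57, alpha 0.05: noncentrality 0.38² × 57 = 8.23, power 80.5%. This is the smallest N that reaches 80%.
- 57 / 0.90 = 63.3, rounded up to 64.

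The stated figures come out with the full 5% given to one outcome. The same noncentrality arises from a group-by-time interaction with d = 0.38 (f = 0.19) and an assumed baseline-to-follow-up correlation of 0.5: 0.19² × 2 / (1 − 0.5) = 0.1444 = 0.38². A paired t-test with a standardised mean change of 0.38 also gives 57. A plain two-group comparison with d = 0.38 does not; it needs 109 per group.

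**3. Family-wise error if any one of the four suffices** (one two-sided 5% test per outcome, no true effect on any):
- Independent tests: 1 − 0.95⁴ = 1 − 0.8145 = 0.1855, or 18.5%.
- Simulated equicorrelated normal statistics (1,000,000 draws per row):

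| Assumed common correlation | Family-wise error |
|---|---|
| 0.2 | 18.0% |
| 0.3 | 17.4% |
| 0.5 | 15.6% |
| 0.7 | 13.1% |
| 0.9 | 9.4% |

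By the Šidák inequality, 18.5% is the ceiling for jointly normal two-sided tests at any correlation. The bound that needs no such assumption is 4 × 5% = 20%.

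**4. Family-wise error under other rules.** If all four must be significant, the chance of a false claim is at most that of any single test, 5%, and no adjustment is needed. If TMT B-A comes first and the others are tested only after it succeeds, the family-wise error is also held at 5%.

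**5. Power cost of Holm.** Holm's first threshold is 0.05 / 4 = 0.0125. With 64 × 0.90 = 57.6 evaluable in total and f = 0.38 (d = 2 × 0.38 = 0.76), the noncentrality is 0.38² × 57.6 = 8.32.
- Alpha 0.05: power 80.9%.
- Alpha 0.0125: power 62.0%.

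If all 64 are analysed, the two figures are 84.9% and 67.9%. To keep 80% power at 0.0125, 81 would have to be analysed; 81 / 0.90 = 90 enrolled.

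**The case against.** **The detail may sit in an analysis plan that is not shown.** The choice between Holm, a hierarchy and a co-primary rule is often made there, and this is a condensed article. That carries some weight. However, the article itself fixes the primaries, the alpha and the sample size. A later plan that adopted Holm would change the power stated here, so the mismatch already lies in the published design.

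**A reader might infer that the plan adopts an any-one-succeeds rule, and so has an 18.5% error rate.** The text does not support that. It neither states nor excludes such a rule. Each test is tied to its own domain, so conclusions domain by domain are equally consistent with it. The 18.5% is conditional on that rule and is a ceiling. Cognitive tests in one sample are likely to be positively correlated, which lowers it.

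**Bonferroni might be meant to span the four primaries.** Its scope is not defined, so this cannot be ruled out. It is the less natural reading, and it would conflict with the sample size section, where 57 reproduces at 0.05 and 81 would be needed at 0.0125.

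**A reader might add the 11 ADAS-Cog items to the count of tests.** The article says only that item scores are recorded. It plans no tests on them, so they are left out here.

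**The power figures depend on an unstated metric.** This is correct. If 0.38 were a plain between-group d, power with 29 per group would be about 30% at 0.05 and 15% at 0.0125 (normal approximation). The family-wise error does not depend on this.

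**Conclusion.** The point stands in a conditional form. The protocol has four unranked primary outcomes, one undivided 5% alpha, no rule across the four, and a sample size built on one of them. If any single significant primary is accepted as evidence of improved cognitive function, the error rate of that claim is above 5%: at most 18.5%, and about 17% to 9% over assumed common correlations of 0.3 to 0.9. Even at 0.9 it is nearly twice the stated rate. These figures assume one two-sided test per outcome, jointly normal statistics and no true effect on any outcome. The excess disappears if all four must succeed or if a hierarchy applies, but the article states neither. It should be settled before the outcome data are analysed, because it determines what the trial may conclude.

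**What to change.** State one rule in the Statistical analysis section before outcome data are analysed. Either option holds the family-wise error at two-sided 5%.

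- **Fixed sequence.** Test TMT B-A, the outcome behind the sample size, first at the full 5%. Test LMT, ADAS-Cog total and TMT-A after it in a pre-specified order, stopping at the first non-significant result. This keeps the planned power for TMT B-A. The cost is that no later outcome can be claimed if TMT B-A fails. The order of the last three is for the investigators to choose.
- **Holm across the four.** Claim improvement only for outcomes that pass. The cost is first-step power of about 62% instead of about 81% with 57.6 evaluable, assuming 0.38 is Cohen's f. Power for a given outcome recovers partly when others are rejected first.

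In the same edit, say what the Bonferroni sentence covers and state the metric of the 0.38. Either rule takes a sentence or two. No extra participants are needed if the lower power under Holm is accepted and stated; restoring 80% at the first Holm step would take 90 enrolled instead of 64.

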### Secondary outcomes

Secondary outcome measures will be plasma biomarkers (BDNF, IL-6, irisin, and FGF21) and physical performance (Timed Up and Go test and 30-second sit to stand test). As for blood collection protocol: twelve-hour fasting blood samples will be collected for 15 ml between 8.00 AM and 9.00 AM and kept in tubes that contain anticoagulants. Blood sampling will be rescheduled if participants report illness or use of anti-inflammatory agents. The participants will be instructed to refrain from exercise, and alcohol for 24 h before each visit. Plasma will be obtained by centrifugation of the blood for 10 min and kept at -80 °C immediately until analysis. Commercially available quantitative sandwich enzyme-linked immunosorbent assay kits will be used for the analysis of BDNF, IL-6, irisin, and FGF21, following the protocols provided by the test manufacturer.

Physical performance assessment will be Timed Up and Go (TUG) single and dual-task and 30-second sit to stand test (30-s CST). For TUG, participants will be instructed to rise from a standard-height chair, walk forward 3 m at their fastest speed, turn 180 degrees at the mark, walk back to the chair, and sit down [46]. The time (in sec) taken to complete the task will be recorded. They will perform: the TUG (single TUG) and the TUG in concurrent with counting backward by three (dual TUG). As for the 30-second sit to stand test, participants will be instructed to sit in the middle of the chair with their back straight, feet flat on the floor, and arms crossed at the wrists, held against the chest. They will be requested to stand up and sit down in the chair repeatedly as many times as possible for 30 s [47]. The total number of sit-to-stands completed within 30 s will be recorded.

### Sample size calculation

The sample size for the study was determined for the primary outcome measures based on previous studies that examined the effects of Tai Chi which could be considered as combined physical-cognitive exercise at low-to-moderate intensity [48, 49]. The previous findings on memory and executive function yielded effect sizes of 0.40 and 0.38, respectively [49]. Thus, the sample size was estimated using the lowest effect size (i.e., executive function). With 80% power and 5% type I error, a total sample size of 57 (29 per group) will be required to detect change. To accommodate 10% dropout, a total of 64 participants (32 per group) will be enrolled in the study.

### Statistical analysis

Data normality will be performed using the Shapiro-Wilk test. Descriptive statistics will be used to describe the demographic characteristics of the participants. If data are normally distributed, the independent samples t-test (for continuous data) and chi-square test (for categorical data) will be conducted to determine differences in demographic data between the intervention and control groups at baseline. A two-way mixed-model ANOVA will be used to compare the outcome measures across the two different assessment intervals (at baseline and the end of 12 weeks) and between the two groups (exercise and control groups). Bonferroni will be used for the post-hoc analysis in this study. However, if data are not normally distributed, non-parametric statistics will be performed. Specifically, the Mann-Whitney U test will be used for pairwise comparisons between groups, and the Wilcoxon signed-rank test will be used to compare the outcome measures between baseline and the end of 12 weeks. Data in this study will be analyzed using the intention-to-treat (ITT) approach. Missing data will be handled using multiple imputations. The alpha level will be set at 5%.

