### Randomization and allocation concealment

Participants meeting the eligibility criteria will be randomly allocated to the exercise or control group. Participants will be stratified by age (60–65, 66–69, 70–75, 76–80, or > 80 years), gender (male or female), education level (≤ 12 or > 12 years), and co-morbidity (1–2, or > 2 types) and randomized using a permuted block randomization with varying block size [4, 6, 8] and 1:1 allocation. Randomization will be administered by an individual external to the study using a computer-generated list and concealed within securely sealed, opaque envelopes. All outcome measures will be performed by trained assessors who are blinded to the participant’s group allocation. The researcher will be blinded to the outcome assessments.

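### The group-by-time mixed ANOVA treats baseline as an outcome, omits the stratification factors and does not name its treatment test; a baseline-adjusted ANCOVA answers the same question and is usually more precise.

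*Protocol article*

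**What the plan says.** The Statistical analysis section names the model for the outcome measures: "A two-way mixed-model ANOVA will be used to compare the outcome measures across the two different assessment intervals", with the levels given as "at baseline and the end of 12 weeks) and between the two groups (exercise and control groups". No covariate is mentioned, and none of the resulting terms is singled out as the test of treatment. If the data are not normal, "the Mann-Whitney U test will be used for pairwise comparisons between groups" and a Wilcoxon signed-rank test compares the two times; both are unadjusted.

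The Assessment and outcome measures section confirms that there are only two measurements: "All assessments will be administered at baseline and post 12-week intervention".

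Under Randomization and allocation concealment, the design uses four factors: "Participants will be stratified by age (60–65, 66–69, 70–75, 76–80, or > 80 years), gender (male or female"), together with "education level (≤ 12 or > 12 years), and co-morbidity (1–2, or > 2 types"). Allocation is by "permuted block randomization with varying block size [4, 6, 8] and 1:1 allocation". None of the four factors reappears in the analysis.

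**The concern.** A two-by-two mixed ANOVA yields three tests, and they answer different questions.

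- **Group by time** compares mean change between groups. With two times it is exactly a t-test on change scores.
- **Group main effect** averages the 12-week difference with the baseline difference, which randomisation makes zero in expectation. It therefore estimates half the treatment effect.
- **Time** is not a treatment effect.

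Only the first is a sensible treatment test, and the section does not say so. Even that term gives baseline a fixed weight of one, whereas ANCOVA estimates the weight from the data and corrects for chance baseline imbalance. Leaving out the factors used to randomise also gives up any prognostic information they carry. Age and education are plausible predictors of cognitive test scores.

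Precision and a clearly identified test are at stake in a trial of 64 people. The validity of the estimate is not.

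**Working it through.** **Inputs from the protocol (Sample size calculation).** Effect size 0.38, metric not stated; 80% power; 5% type I error; 57 evaluable in total (29 per group); 10% dropout; 64 enrolled. Expected evaluable: 64 × 0.9 = 57.6, or 28.8 per group.

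**Assumed.** r, the correlation between baseline and 12-week values, is not given. The range 0.3 to 0.9 is shown.

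**Reproducing the planned size.** Read 0.38 as Cohen's f in a one-degree-of-freedom between-group F test, with non-centrality N × 0.38². Power is 0.798 at N = 56 and 0.805 at N = 57, so 57 is reproduced, and 57/0.9 = 63.3 rounds up to 64. Read as a standardised mean difference, 0.38 would need 109 per group two-sided, which does not reproduce. For two equal groups d = 2f = 0.76. This value is inferred; the protocol does not state it.

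**Large-sample variance, baseline covariate only.** With equal SDs at both times and in units of the 12-week variance:

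- change score: 2(1 − r)
- ANCOVA on baseline: 1 − r²
- ratio: (1 − r²)/[2(1 − r)] = (1 + r)/2, so the reduction is (1 − r)/2

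**Cost of covariates.** The proposed model has q = 5 covariate terms: baseline, continuous age, gender, education and co-morbidity. The approximate variance inflation is 1 + q/(N − q − 3). At N = 58 this is 1 + 5/50 = 1.10; at N = 57.6 it is 1 + 5/49.6 = 1.101. The net reduction is 1 − 1.101 × (1 + r)/2 if the four factors add nothing beyond baseline. It is 1 − 0.9 × 1.101 × (1 + r)/2 if they explain 10% of the remaining variance.

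| r | Baseline only, large sample | Five covariates, factors add nothing | Five covariates, factors explain 10% |
|---|---|---|---|
| 0.3 | 35% | 28% | 36% |
| 0.5 | 25% | 17% | 26% |
| 0.7 | 15% | 6% | 16% |
| 0.8 | 10% | 1% | 11% |
| 0.9 | 5% | −5% | 6% |

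**Age in bands.** The design has 5 × 2 × 2 × 2 = 40 strata for 64 participants, or 1.6 each, so only main effects are feasible. Entering age in its five bands makes 4 + 1 + 1 + 1 = 7 stratum terms. If they add nothing, the net figures fall to about 24%, 12%, 0.5%, −5% and −11%. This is why age is better entered as a continuous term.

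**Power.** Take d = 0.76 in SDs of the 12-week score, 28.8 per group, two-sided 5%. The non-centrality is 0.76 × √(28.8/2) = 2.884, divided by the square root of the variance above.

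| r | Change (group by time) | ANCOVA, baseline only | ANCOVA, five covariates, factors add nothing |
|---|---|---|---|
| 0.3 | 67% | 84% | 81% |
| 0.5 | 81% | 91% | 88% |
| 0.7 | 96% | 98% | 97% |

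The last column also divides the non-centrality by √1.101 and uses 57.6 − 7 = 50.6 degrees of freedom. At r = 0.5 the change variance is 2(1 − 0.5) = 1, so the change test has the power of an unadjusted comparison of 12-week values. Below about r = 0.5 it misses the 80% target.

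**The case against.** The best defence is that this is a choice about efficiency and that the plan contains no error. Under randomisation the group-by-time contrast estimates the same effect as ANCOVA without bias. Omitting stratification factors at worst makes the test conservative, and with 1.6 participants per stratum and blocks of 4 to 8, most blocks would be incomplete, so even that conservatism is partial. On the inferred effect size the planned test already reaches 81% power at r = 0.5 and 96% at r = 0.7. The effect size has no stated metric; had it been defined on change scores, the power of the change test would not vary with r. All of this stands, and it limits the size of the point.

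It may also be said that naming the decisive term and the covariates belongs in the statistical analysis plan. That is fair for the missing name of the term. It does not answer the main point, because the protocol does state a model, and that model makes baseline an outcome.

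Three stronger readings are tempting, and the protocol does not support them.

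- A reader might infer that ANCOVA saves 15% to 35% of the variance at no cost. That range belongs to the baseline covariate alone at assumed r of 0.7 to 0.3. The covariates use degrees of freedom, and at r = 0.9 the full model can lose slightly.
- A reader might infer that treatment will be judged by the group main effect, whose power would be 34% to 42% at r of 0.7 to 0.3. The protocol never names that term as its test, and sizing the trial to detect change points towards group by time.
- A reader might infer that the planned estimate is biased. It is not.

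**Conclusion.** The point holds as a recommendation on efficiency and clarity. The stated model uses baseline as an outcome, leaves out all four stratification factors and does not identify its treatment test. A baseline-adjusted ANCOVA estimates the same effect with variance lower by (1 − r)/2 in large samples.

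The size depends on r, which the protocol does not give, and on how prognostic the four factors are, which is unknown. The benefit is substantial at r of 0.5 or less and small at 0.8 or more. The worst case in the range examined is a loss of about 5%. The power figures also rest on reading 0.38 as Cohen's f and on expressing the effect in SDs of the 12-week score. The recommendation itself does not depend on either reading. The change should be made before outcome data are analysed.

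**What to change.** Replace the mixed ANOVA as the primary analysis of each outcome with a linear model of the 12-week value on group, baseline value, age (continuous), gender, education stratum and co-morbidity stratum, as main effects only. Report the adjusted group difference with its 95% CI as the single treatment test for that outcome, and keep the mixed ANOVA as supportive.

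Two details need settling with it. The switch to unadjusted rank tests after a normality check should not be able to displace this model as the primary analysis. The co-morbidity strata start at one condition, so the protocol should say how a participant with none is classified before the factor is used as a covariate.

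The cost is a change of wording and five covariate degrees of freedom. All the variables are already collected at baseline, and the sample size need not change on this account.
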